## Abstract

Early Childhood Education and Care (ECEC) settings are important environments to support children’s physical activity (PA). In 2021, COVID-19 regulations recommended the provision of indoor–outdoor free-play programs in ECEC settings to reduce the transmission of COVID-19, resulting in an increased uptake of this practice. As the context has since changed, research suggests that ECEC services could cease the implementation of these practices. Therefore, this pilot randomised controlled trial (RCT) aims to examine the feasibility, acceptability, and impact of a sustainment strategy to ensure the ongoing implementation (sustainment) of ECEC-delivered indoor–outdoor free-play programs. Twenty ECEC services located in New South Wales, Australia that have implemented indoor–outdoor free-play programs since the release of COVID-19 guidelines will be recruited. The services will be randomly allocated either the sustainment strategy or usual care. The “Sustaining Play, Sustaining Health” program consists of eight strategies, developed to address key barriers against and facilitators of sustainment informed by the Integrated Sustainability Framework. The outcomes will be assessed via internal project records, staff surveys, and a self-reported measure of free play. This study will provide important data to support the performance of a fully powered trial within Australian ECEC settings and to inform the development of future sustainment strategies.

## 1. Introduction

Globally, physical inactivity is the fourth leading risk factor for mortality, contributing to approximately 3.2 million deaths each year and accounting for 198.4 disability-adjusted life years (DALYs) per 100,000 people [1,2]. In Australia, 2.5% of the total disease burden is due to physical inactivity and contributes to 10–20% of the individual disease burden from chronic disease such as diabetes, cardiovascular disease, and cancer [1,3]. Additionally, evidence suggests that physical activity (PA) in childhood tends to track into adulthood [4,5,6,7], reducing the risk of chronic diseases later in life [8]. The World Health Organisation (WHO) recommends that children aged 3–4 years should spend at least 180 min active per day, of which at least 60 min should be moderate-to-vigorous physical activity (MVPA) [9]. However, in Australia, only about 6 in 10 (61%) children aged 2–5 met the PA guidelines in 2018 [10]. Similarly, a 2022 meta-analysis of 63 studies from 23 countries found that only 11.26% of pre-schoolers and 10.31% of children adhered to the 24-Hour Movement Guidelines [11]. Therefore, governments internationally recommend the delivery of public health programs and initiatives that focus on increasing the time young children spend being physically active [12].

Early Childhood Education and Care (ECEC) settings are important settings to reach young children with PA-promotion efforts [13,14,15]. As children aged 3–5 years spend an average of 25–35 h a week in ECEC services, these settings provide a broad scope for intervention delivery to increase child activity at the population level [16]. It is recommended internationally and in Australia that ECEC services provide sufficient opportunities for outdoor free play [12]. Further systematic-review and randomised controlled trial (RCT) evidence support the effectiveness of outdoor free-play opportunities in improving child MVPA [17,18]. In particular, indoor–outdoor free-play programs are recommended as ways of increasing outdoor free play [17]. This refers to periods of free play located in both indoor and outdoor environments, with children able to move freely between the two. Our national study with 203 Australian services shows that approximately 60% of ECEC services implemented indoor–outdoor free-play programs between December 2017 and August 2018 [19].

In 2021, in response to the Coronavirus (COVID-19) pandemic, state education authorities in Australia released guidance for ECEC services that included recommendations to services to “consider operating an indoor–outdoor program for the full day/session” and to “encourage appropriate outdoor programs to support social distancing” [20]. This is likely to have resulted in an increased implementation of indoor–outdoor free-play programs. For example, our unpublished data with over 200 Australian ECEC services found that the amount of indoor-only free-play time provided per day reduced from 145 min to 93 min, and that indoor–outdoor free-play programs increased this provision from 71 min to 230 min between 2017/2018 and 2021/2022. Whilst this increase is encouraging, studies examining the effects of public health policies suggest that behaviours are likely to attenuate once acute exposure to the change in stimuli is removed or following the withdrawal of recommendations [21,22,23,24]. Similarly, as the guidance around COVID-19 for ECEC services has now eased [20], we hypothesise that the implementation of indoor–outdoor free-play programs may also attenuate. 

Ensuring indoor–outdoor free-play programs are sustained is crucial to guaranteeing that the ongoing health benefits for children can continue to be achieved [25]. There is, however, a lack of research examining how to sustain the delivery of public health interventions in community settings. Our overview of four Cochrane reviews found no randomised or non-randomised trials that assessed interventions to improve the sustainment of programs targeting PA, nutrition, smoking and alcohol in community-based settings (including ECEC settings, schools, sporting clubs and workplaces) [24]. Therefore, to develop the evidence base and inform the performance of a fully powered trial, we sought to assess the feasibility, acceptability, and impact of a sustainment strategy to improve the continued delivery of indoor–outdoor free-play programs: the ‘Sustaining Play, Sustaining Health (SPSH)’ program.

Specifically, the aims of this research are to assess the:(i)Acceptability, feasibility, and impact of the SPSH program for the sustainment of indoor–outdoor free-play programs (for this trial, defined as the ongoing implementation of evidence-based practice) in ECEC services;(ii)Feasibility of trial methods to inform the performance of a fully powered RCT;(iii)Barriers and facilitators to the sustainment of indoor–outdoor free-play programs in ECEC services.

## 2. Materials and Methods

### 2.1. Design and Setting

The study will employ a 6-month pilot, parallel group RCT design, using guidance on undertaking pilot implementation trials outlined by Pearson et al. [26] and reporting in accordance with the Consolidated Standards of Reporting Trials (CONSORT) pilot guidance [27]. Twenty ECEC services located in New South Wales (NSW), Australia (excluding one region participating in another trial to increase outdoor free play) who report having implemented indoor–outdoor free-play programs for most of the day since July 2021 (i.e., defined as <20% of indoor-only free-play time during core service-operating hours) will be randomised to receive either the SPSH program or usual care. July 2021 was selected as the programs initiation date as this was when guidance around outdoor-free-play programs for ECEC services was released by state education authorities. 

### 2.2. Participants and Recruitment

#### 2.2.1. Sampling Frame

The research team undertook a telephone survey with a randomly selected sample of 231 Long Day Care (LDC) services and preschools in NSW from October 2021 to June 2022, of which 99 services met the eligibility criteria for the current study and form the current sampling frame. These LDC services usually operate from 7 a.m. to 6 p.m. Monday through Friday and cater for children from birth to school age, while preschools cater for children aged 3–5 years and operate from 9 a.m. to 3:30 p.m. [28].

#### 2.2.2. Eligibility

To be eligible to participate, ECEC services needed to report the implementation of indoor–outdoor free-play programs for most of the day (i.e., offering indoor-only free play for only 20% or less of their core operating hours, during which most their children are present in care. This can be defined as approximately 84 min or less, as standard operating hours are between 8:30 a.m. and 3 p.m.) on a typical day since the introduction of the COVID-19 guidance for ECEC services (July 2021) [29]. A typical day represents a day in which excursions or events which may disrupt the service’s usual routine are not planned. Services were considered ineligible if they: (i) had implemented indoor–outdoor free-play programs prior to the introduction of the COVID-19 guidance (July 2021); (ii) catered exclusively for children with special needs; (iii) had a nominated supervisor or staff who did not understand English; or (iv) were a Department of Education community-run service (representing less than 5% of services) across NSW. 

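### The 84-minute eligibility cut-off is not 20% of the stated core hours (that would be 78 minutes), and the protocol gives the limit as both below 20% and 20% or less

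*Protocol article*

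**What the plan says.** Section 2.2.2 (Eligibility) of the protocol article sets the main inclusion rule as a proportion: "offering indoor-only free play for only 20% or less of their core operating hours". It then gives a minute equivalent and the basis for it: "This can be defined as approximately 84 min or less, as standard operating hours are between 8:30 a.m. and 3 p.m".

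Section 2.1 (Design and Setting) states the same limit with a different inequality: "defined as <20% of indoor-only free-play time during core service-operating hours".

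Section 2.2.1 (Sampling Frame) gives two other sets of hours. For long day care, "These LDC services usually operate from 7 a.m. to 6 p.m. Monday through Friday"; for the other service type, "preschools cater for children aged 3–5 years and operate from 9 a.m. to 3:30 p.m". The same section says that a telephone survey reached 231 services, "of which 99 services met the eligibility criteria for the current study and form the current sampling frame". Section 2.2.3 (Recruitment Procedures) has eligibility assessed again in a recruitment survey.

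**The concern.** The minute figure is presented as following from the percentage and the hours, but it does not follow from them. The article therefore carries three versions of one rule that are not equivalent: below 20%, 20% or less, and about 84 minutes or less.

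This rule defines the trial population. It decides which services count as already delivering the practice whose sustainment is to be tested, and it underlies the 99-service frame. If the versions differ, a reader cannot tell exactly which services were eligible, another team cannot reproduce the selection, and the ambiguity would pass into the fully powered trial that this pilot is meant to inform.

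**Working it through.** **Inputs**
- Limit: 20% of core hours (2.2.2); strictly below 20% in 2.1.
- Stated minute equivalent: about 84 (2.2.2).
- Hours given as its basis: 8:30 a.m. to 3 p.m. (2.2.2).
- Other hours in the article: preschools 9 a.m. to 3:30 p.m.; long day care 7 a.m. to 6 p.m. (2.2.1).

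**Attempt to reproduce 84.** Formula: cut-off = 0.20 × length of day in minutes.

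| Basis | Length of day | 20% of it | 84 min as a share |
|---|---|---|---|
| 8:30 a.m. to 3 p.m. (the stated basis) | 6.5 h = 390 min | 78 min | 84/390 = 21.5% |
| Preschool hours | 6.5 h = 390 min | 78 min | 21.5% |
| Long day care hours | 11 h = 660 min | 132 min | 84/660 = 12.7% |

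No set of hours in the article gives 84.

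**Working backwards.** 84 / 0.20 = 420 min = 7 h. A day from 8:30 a.m. to 3:30 p.m., or from 8 a.m. to 3 p.m., would have that length. The article states neither.

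**Size of the discrepancy.** 84 − 78 = 6 min a day, which is 6/78 = 7.7% of the limit that the stated hours imply. In proportions it is 21.5% − 20.0% = 1.5 percentage points.

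**Who is classified differently.** A service reporting m minutes exceeds 20% when its core day is shorter than m / 0.20.
- At m = 79 this means a core day shorter than 395 min.
- At m = 84 it means a core day shorter than 420 min.
- With the stated 390-minute day, every value above 78 and up to 84 min passes the minute rule and fails the percentage rule.
- With a core day of 420 min or longer, 84 min is within 20% and this conflict does not arise.

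**Inequality.** The wordings in 2.1 and 2.2.2 differ only for a service at exactly 20%.

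**The case against.** The strongest reply has four parts.

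1. **The minute figure is only approximate.** This does not rescue it. The product of the stated inputs is exactly 78, so nothing needed rounding, and 84 is exactly 20% of a different day. That pattern points to a wrong input.

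2. **The governing rule is the percentage, applied to each service's own core hours, and the minutes only illustrate it.** This is a fair reading and it stands in part. The article does not say whether the telephone survey or the recruitment survey applied the percentage or the minutes. A reader might infer that services above 20% were in fact enrolled. The article does not support that, because it reports no service between 78 and 84 minutes. Nor can the gap be sized from the average of 93 minutes of indoor-only play that the Introduction reports for 2021/2022: no spread is given, and the figure is not said to refer to core hours.

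3. **The trial's comparison is not harmed.** This stands. Any borderline service was randomised like the rest, section 2.6.2 compares groups with adjustment for baseline, and the pilot has 20 services and no efficacy-based sample size. A reader might also take the cut-off as the benchmark for having sustained the practice at follow-up. The article sets no such benchmark: sections 2.5.1 and 2.6.2 treat the impact outcome as total minutes, with no split at 20%, 78 or 84.

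4. **The hours may be the slip, with 84 the intended figure.** This also stands. The article does not settle it, so 78 cannot simply be declared the right limit.

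**Conclusion.** The threshold is inconsistent as written. With the stated hours, 20% is 78 minutes; the printed 84 minutes is 21.5% of those hours and fits only an unstated 420-minute day. The two sections also disagree on whether exactly 20% qualifies.

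The size is 6 minutes a day, or 1.5 percentage points. The consequence is limited to what the text permits: a service with a 390-minute core day and more than 78 and up to 84 minutes could enter under the minute rule while exceeding the percentage rule. Whether any did is not shown.

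The conclusion rests on taking the stated hours as the basis for the minute figure, as the sentence in 2.2.2 does. It does not depend on which of the two numbers is the error. The point matters for a clear, reproducible definition of the population and for the next trial's criteria. It does not indicate bias in the between-group comparison.

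**What to change.** - Reconcile the percentage, the minutes and the hours in 2.2.2. If 8:30 a.m. to 3 p.m. stands, the equivalent is 78 minutes. If 84 minutes was intended, correct the hours to the 420-minute day that it implies.
- Use one inequality in both 2.1 and 2.2.2.
- State whether screening applied the percentage of each service's own core hours or the fixed number of minutes.
- Check the recruitment-survey data already held, and report how many services recorded more than 78 and up to 84 minutes, with their core hours where available.
- Keep every service as randomised, in line with the intention-to-treat principle in 2.6.2.
- Carry the reconciled rule into the eligibility criteria of the fully powered trial.

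The cost is a text correction and a short check of existing records, with no new data collection. At most, a few services may have to be described as lying above 20%. As the trial is already in the intervention-delivery stage, the correction can go into the registration record and the results report, where section 3 (Trial Status) already places modifications and deviations.

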#### 2.2.3. Recruitment Procedures

All services in the sampling frame will receive an invitation email consisting of a recruitment package including an information statement and a link to an online consent form outlining study requirements and requesting participation. Once the consent form has been completed by the nominated supervisor, the online survey will automatically generate the recruitment survey to assess eligibility. A member of the research team will telephone services that have not responded after two weeks of receiving the email to discuss study details, confirm eligibility and request consent for study participation. Recruitment will continue until 20 ECEC services have consented [30,31]. Additionally, the research team will obtain the contact details of an educator who will assist with baseline data-collection processes. 

### 2.3. Randomisation and Blinding

Following baseline data collection, services will be randomly allocated to either receive the SPSH program or usual care. A statistician will set up block randomisation using a computerised random number generator. Block randomisation will be used to ensure group allocation is approximately equal. This will be uploaded onto the online data-capturing platform (REDCap) [32,33], where service records are stored and concealed from statisticians. This pilot RCT will be conducted as an open trial as the sustainment strategy cannot be delivered without revealing the allocation to services. Therefore, services and data collectors will not be blinded to group allocation; however, those conducting data analysis will remain blinded to allocation for the main impact outcome (minutes of outdoor free play).

### 2.4. Intervention

#### 2.4.1. Theoretical Framework

The development of the 6-month sustainment strategy to increase sustainment of indoor–outdoor free-play programs was overseen by an advisory group consisting of implementation and behavioural scientists, health-promotion staff and health policymakers; it was informed by the Integrated Sustainability Framework developed by Shelton et al. [25]. The Integrated Sustainability Framework is a comprehensive, theoretically informed sustainability-determinants framework developed based on available empirical research on factors identified as influencing intervention sustainment across a range of contexts. The framework outlines the dynamic interactions between 21 multi-level factors across five domains, including: Outer Contextual Factors, Inner Contextual Factors, Processes, Characteristics of the Interventionists and Population and Characteristics of the Intervention [25]. To identify the determinants related to the sustainment of PA programs, data were collected from a telephone survey with ECEC services nationally assessing the Integrated Sustainability Framework constructs and extracted from a systematic review of sustainability determinants within ECEC and school settings [34].

From this data, we identified 20 barriers associated to the sustainment of PA programs in the ECEC and school settings, which mapped to all five domains of the Integrated Sustainability Framework. This resulted in the development of eight strategies (see Table 1) that sought to address these barriers and support the sustainment of implementing indoor–outdoor free-play programs. As barriers were predominantly mapped to the outer contextual factors (e.g., lack of future external funding/financial support, or lack of state requirements) and processes domains (e.g., lack of training/professional development opportunities to upskill, or lack of collaboration with community groups), these domains were of particular focus when developing the strategies. The Expert Recommendations for Implementing Change (ERIC) glossary adapted to describe strategies to address sustainment [35] was used to select the strategies, including: (i) identifying an opinion leader to act as a key driver of the sustainment strategy; (ii) affirming the service’s intent to continue; (iii) providing the service with technical support and educational resources to self-direct the sustainment strategy; (iv) developing a formal sustainment blueprint; (v) engaging with family and community members; (vi) reviewing and changing service policy to integrate indoor–outdoor free-play programs; and (vii) developing an ongoing monitoring plan to self-direct the sustainment of the evidence-based practice (EBP) well after the intervention period [36]. The intervention-mapping process is outlined in Table 1, below.

#### 2.4.2. Sample Size

As this is a pilot study, a formal sample-size calculation on efficacy was not performed, in line with best-practice guidance [27]. However, the researchers sought to recruit 20 ECEC services, as this number was considered feasible in the timeframe and sufficient to provide an adequate indication of the feasibility and acceptability of study methods and the sustainment strategy [30,31].

#### 2.4.3. Intervention Components

Following baseline-data collection and randomisation, services allocated to the intervention group will receive the sustainment strategy. Specifically, services will be supported to continue to implement indoor–outdoor free-play programs.

The delivery of the SPSH program will include a minimum of four remotely delivered scheduled contacts, including two meetings via video calls and two support emails (see Table 2). The use of video calls has been found to be an effective and acceptable modality of delivering behaviour-change interventions for this type of setting as an alternative to face-to-face contact [56,57]. Contacts will target the nominated supervisor and an educator responsible for supporting the implementation of PA programs in the ECEC service. The intervention will be delivered by experienced health-promotion officers (HPO) employed by a local health-promotion unit with tertiary qualifications in physical activity, health promotion, nutrition and dietetics. They are employed by the local health services and have extensive experience supporting ECEC services in the delivery of healthy-eating and physical-activity programs. Additionally, the HPOs have undertaken behaviour-change training with an expert behavioural scientist to support behaviour change in this setting.

(a)Identify opinion leaders at the service:

ERIC Strategy: *Engage with local opinion leaders (i.e., supervisors or room leaders)*

Barriers Targeted: *Lack of administrative buy-in and support/leadership/management and lack of program leaders/facilitators/champions.*

Engaging with opinion leaders is an important strategy to understand the existing internal support for the EBP within the service and is a key driver of implementation in ECEC settings [58,59,60,61]. The ECEC services will be asked to identify any colleagues who they believe are drivers of implementation or “educationally influential”. These may be the nominated supervisor or another existing staff member, such as a room leader. If this is not the nominated supervisor, this person will be invited to participate in service contacts along with the nominated supervisor/service manager. The HPO will determine the existing roles and influence of these staff members in current implementation processes as a component of the first 30–60-min introductory-meeting video-call contact. The SPSH program will be discussed and additional roles or tasks for these key staff members will be co-developed as part of the process of undertaking a “Sustainability Action Plan” (see strategy d for further detail). 

(b)Affirm intent of continuity:

ERIC Strategy: *Affirm formal commitments*

Barriers targeted: *Lack of motivation/interest, limited cost-effectiveness/feasibility of program, time required to implement and record uptake of the program and competing resources, responsibilities and curriculum demands.*

This strategy aims to assess whether commitments are being upheld and whether new commitments are required to help sustain the intervention [35]. Services will be supported in affirming the service’s intent to continue and readiness for the long-term implementation of the EBP. To this end, the HPO will explicitly ask the nominated supervisor and the opinion leader questions regarding their intention to continue the implementation of their current indoor–outdoor free-play programs during the introductory-meeting video call and 3-month support-meeting video call. To explore the likelihood of the services being able to sustain long-term change, the HPO will also ascertain the motivations behind the services’ original implementation, determine any barriers to and facilitators of the ongoing implementation of EBP and the readiness to implement the SPSH program to enhance integration into typical care. As part of supporting a commitment to long-term change, the HPO will help services draft ideas for a formal “motivational statement” for the implementation of the EBP. The services will be helped to use this as part of their staff and community communications, as well as for inclusion in policy and procedure updates, as appropriate.

(c)Provide local technical assistance to support integrating strategies:

ERIC Strategy: *Provide local technical assistance*

Barriers targeted: *Lack of training/professional development opportunities to upskill and lack of clear data on effectiveness of program.*

This strategy was previously found to support the implementation of ECEC-based interventions and to be effective in improving implementation, staff motivation and problem solving within these interventions [62,63,64]. The HPOs will provide local technical assistance in the form of two 30–60-min video calls from the HPO and a minimum of two action-oriented emails throughout the intervention period to assist them in implementing the SPSH program. Video calls will occur at months one and three, with policy reviews via email sent out at months two and four–five. Each contact will draw on continuous quality-improvement principles to review progress on the “Sustainability Action Plan” and provide feedback on the integration of sustainment strategies. The first video call will occur after recruitment and will focus on introducing the SPSH program, explaining the roles of the opinion leader and the nominated supervisor (see a), understanding any determinants of sustainability for the service (see b) and discussing the development of the “Sustainability Action Plan” (see d). The second video call will take place at the 3-month time point and will focus on the service’s progress with its “Sustainability Action Plan” and any challenges experienced. The two emails will consist of providing feedback on the service’s policy through the use of a template and suggestions for amendments (see g). Additional support contacts may occur at time points outside of those specified if further support is required and will be recorded as part of adaptations to the SPSH program. 

(d)Develop a formal sustainment blueprint:

ERIC Strategy: *Develop a formal implementation blueprint*

Barriers targeted: *Lack of centralised coordination and absence of plans with defined measures.*

Similar strategies haves been used in previous implementation interventions to facilitate improvement in implementation within ECEC services [65]. Services will be supported to develop an action plan (blueprint) for the service to implement the SPSH program. This will support the identification of strategies to be put in place as well as sustainment strategies that may have already been undertaken (fully or partially). Examples of strategies include notifying families, community members and staff of indoor-outdoor free play programs, updating the service policy, and conducting indoor-outdoor free play programs as part of the daily routine. Progress with the plan will be monitored during the 3-month support meeting video call, and adjustments and/or support will be provided to help meet strategies, as required.

(e)Distribute educational materials to support ongoing implementation:

ERIC Strategy: *Distribute educational materials*

Barriers targeted: *Lack of future external/financial support, lack of state requirements, lack of evidence-based treatments, government perceptions, lack of training/professional development opportunities to upskill and lack of clear data on effectiveness of program.*

Distributing educational materials to services has been found to be highly acceptable among ECEC service staff and is commonly used as part of multicomponent implementation interventions [65,66,67]. Services will be provided with a resource pack approximately 3 days prior to the introductory meeting video call. It will consist of resources developed or adapted from materials previously used by the research team to increase outdoor free-play opportunities. The resources are intended to target barriers to sustainment and support implementation of the “Sustainability Action Plan”. Resources include fact sheets on external organisations that support outdoor free play, how outdoor free play aligns with the sector-accreditation standards, a summary of the COVID-19 guidelines relating to outdoor play, Australian PA guidelines, family and staff templates to include as part of orientation packages, a service-policy template and tips for maintaining indoor–outdoor free-play programs across all seasons. Further resources will be developed and provided, tailored to the service’s specific needs. 

(f)Engaging with family members:

ERIC Strategy: *Involve patients/consumers and family members*

Barriers targeted: *Lack of collaboration with community groups, communicating information to stakeholders, lack of parental buy-in/support and staff turnover.*

Engaging with family members and communities is critical to support initial adoption and implementation of programs [45,68]. This strategy will include the provision of resources such as 6 newsletter-communication snippets providing information around the benefits of outdoor free play, outdoor play in various seasons and outdoor play and COVID-19. These are to be used in service-provided family newsletters or other communication channels at the service’s discretion, with a minimum requirement of 1 newsletter snippet to be sent out throughout the 6-month SPSH program. A template for the inclusion of indoor-outdoor free play programs in the family-orientation package will also be provided. Services will be asked to distribute these using their usual communication channels.

(g)Reviewing and embedding change into policy:

ERIC Strategy: *Mandate change*

Barriers targeted: *Absence of plan with defined measures, lack of centralised coordination and lack of training/professional development opportunities to upskill.*

Implementing a written policy around PA has been associated with higher levels of PA [69,70,71]. This strategy aims to ensure that the commitment to sustain indoor–outdoor free-play programs is reflected in a relevant service policy. At the 2-month- and 4–5-month-timepoint contacts, the HPO will review each service’s policy and suggest potential changes to promote the continuation of indoor–outdoor free-play programs.

(h)Develop an ongoing monitoring strategy:

ERIC Strategy: *Develop and implement tools for quality monitoring*

Barriers targeted: *Accuracy in assessing impact of program, lack of clear data on effectiveness of program and absence of plan with defined measures.*

Ongoing monitoring is important to allow services to continue to determine whether they are implementing the program as intended [72]. Services will be encouraged to develop their own plan during the intervention contacts with the HPOs to ensure the EBP continues to be implemented long term. Alternatively, services can continue to use a tool provided by the research team as a way of continuing to document implementation twice a year. 

